## Abstract

**Background:**

Follow-up care after kidney transplantation is performed in transplant centers as well as in local nephrologist’s practices in Germany. However, organized integrated care of these different sectors of the German health care system is missing. This organizational deficit as well as non-adherence of kidney recipients and longterm cardiovascular complications are major reasons for an impaired patient and graft survival.

**Methods:**

The KTx360° study is supported by a grant from the Federal Joint Committee of the Federal Republic of Germany.

The study will include 448 (39 children) incident patients of all ages with KTx after study start in May 2017 and 963 (83 children) prevalent patients with KTx between 2010 and 2016.

The collaboration between transplant centers and nephrologists in private local practices will be supported by internet-based case-files and scheduled virtual visits (patient consultation via video conferencing). At specified points of the care process patients will receive cardiovascular and adherence assessments and respective interventions. Care will be coordinated by an additional case management.

The goals of the study will be evaluated by an independent institute using claims data from the statutory health insurances and data collected from patients and their caregivers during study participation. To model longitudinal changes after transplantation and differences in changes and levels of immunosuppresive therapy after transplantation between study participants and historical data as well as data from control patients who do not participate in KTx360°, adjusted regression analyses, such as mixed models with repeated measures, will be used. Relevant confounders will be controlled in all analyses.

**Discussion:**

The study aims to prolong patient and graft survival, to reduce avoidable hospitalizations, co-morbidities and health care costs, and to enhance quality of life of patients after kidney transplantation.

**Trial registration:**

ISRCTN29416382 (retrospectively registered on 05.05.2017)

## Background

Kidney transplantation (KTx) is the therapy of choice for patients with end stage renal disease and is associated with significantly reduced morbidity and mortality compared to dialysis.

In the first 3 years after KTx about 8% of the patients lose their graft. This increases steadily over the following years [1]. The main reasons for graft loss are chronic rejections and death with functioning graft due to cardiovascular events and non-adherence to the prescribed medication regimen. Several cohort studies by us and others confirmed that about one third of graft losses per year are due to non-adherence [2–4]. Adolescents experience a significant increase of graft failure during the transition phase to adult care.

Currently, post-transplant care in Germany is split between outpatient services of the hospital transplant centres and (pediatric) nephrologists in private practices usually located close to the patient’s place of residence. KTx360° aims to establish a structured post-transplant care program integrating health care providers from different sectors of the German health system including hospital transplant centers, (pediatric) nephrologists in private practice, and other health professionals relevant for patient care such as transplant nurses, psychologists or sports medicine specialists.

## Methods/design

Inclusion criteria for this study are: KTx from 2010 to 2019 that was performed at one of the two kidney transplantation centres in the German state of Lower Saxony, study participation of the (pediatric) nephrologist responsible for the patient’s follow-up, and membership of the patient in a participating statutory health insurance. Patients of all ages can be included.

Two cohorts of patients will be included in KTx360°: incident and prevalent patients. Incident patients will have their kidney transplantation during the recruitment period of the study (2017 to 2019) at one of the two transplant centers in Lower Saxony. There are about 225 kidney transplantations per year in these centers (210 adults and 15 children/adolescents). Assuming a response rate of 80% caused by non-participation of health insurances, private practice nephrologists or patients who decline participation, we expect to include a total sample of *n* = 487 (*n* = 448 adults, *n* = 39 children/ adolescents) incident patients during the 31 months recruitment period. With a rolling recruitment process and an assumed 15% drop-out rate per year due to graft loss, death or withdrawal from the study we expect to obtain data from 286 adults and 26 children/adolescents completing 2 years post-transplant observation and of 121 adults and 12 children/adolescents with three post-transplant years. Prevalent patients who had their kidney transplantation between 2010 and 2016 will be included in the study when they attend their regular follow-up care visits at the transplant centers. Under similar conditions as the incident patients and an assumed 5% mortality rate per year for adults before study inclusion, we expect a total of *n* = 1046 prevalent patients (*n* = 83 children/adolescents) to participate in the study.

Study patients can be compared with two different control groups based on claims data. The first control sample comprises historical data of the prevalent patients enabling comparisons between post-transplant care before and after implementation of KTx360° for patients of the two kidney transplant centres in Lower Saxony (historical comparison group). Second, all participating health insurance companies will provide claims data of their insurants who received a kidney transplantation in a non-participating German transplant centre between 2010 and 2019 (external comparison group). In Germany, there are 2074 kidney transplantations per year [5] with about 5% of transplantations in children or adolescents under the age of 20 years. Taking into account 10% of patients with private health insurances, a response rate of 70% (because not all statutory insurances are participating) and a mortality rate of 5% per year for adults, results in available data of about 12,413 patients in their first year after transplantation. Subtracting the number of study participants (*n* = 1533), we expect to receive claims data on about *n* = 11,533 patients with kidney transplantations in the external comparison group.

An a-priori power analysis for the primary outcome of a 20% reduction of health care costs due to hospitalizations (see section on endpoints below) was conducted based on data of one statutory health insurance. According to these data, average costs of hospital treatments in the first 2 years after transplantation are estimated 19,000 € per patient. The power analysis for the effect of a 20% reduction (two-sided test) was performed in SAS 9.3 under the following assumptions: pooled standard deviation of 10,000, normal distribution, and α = .05. With the expected sample size in year one and two after transplantation of *n* = 286 incident adults, a power of .995 was estimated to find the assumed difference. Thus, we expect sufficient power to detect the hypothesized effect.

The main focus of the trial is the long-term improvement in post-transplant patient management by the introduction of eHealth elements and additional integrated therapeutic options. With the involvement of case managers we intend to facilitate the cooperation between transplant centers, nephrologists in private practice, and patients. The establishment of an internet-based case file that can be used by all three parties should further optimize communication, cooperation, and thereby post-transplant care. Especially the possibility for our patients to have personal access to their health data is an innovation that will enhance transparency and self-management abilities. Substituting several face-to-face follow-up visits at the transplantation centres by video consultations in the offices of the (pediatric) nephrologists is supposed to reduce travel costs and may avoid doubling of lab examinations. Based on risk assessments, specific interventions will be offered that enhance health behavior and improve adherence to immunosuppressant medication (IS) and reduce cardiovascular risk. The study design is summarized in Fig. 1.

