Exercise recommendations in transplant recipients include endurance training 2–4 times per week (improving vascular function, reduced cardiovascular risk) and regular resistance training (to prevent osteoporosis and skeletal muscle loss) [15]. In KTx360° a regular home based exercise training program will be implemented. Initiated 2–3 months after transplantation patients (including criteria are duration of dialysis longer than 3 years, coronary artery disease, diabetes mellitus, BMI > 35, patients under the age of 18 years) will perform a physical examination and an incremental exercise testing on an ergometer including blood lactate measurements for determination of cardiovascular and skeletal muscle function. Furthermore, a 30 min constant load test on a cycle ergometer with ECG, blood pressure, blood lactate and glucose monitoring, a Timed up and go test, a Sit-to-Stand-test and measurement of steps per day will be performed initially and every 12 months for evaluation of secondary outcome parameters. Exercise training recommendations are derived from exercise intervention studies with heart and renal transplant patients and include moderate endurance training or moderate resistance training every other day:Exercise capacity near to normal (>80% of normal values): Initial duration 15-30 min with 35–60% of maximum exercise capacity.Exercise capacity reduced (60–80% of normal values): Initial duration 10-20 min with 30–50% of maximum exercise capacity.Exercise capacity reduced (<60% of normal values): Initial duration 15-20 min with 25–40% of maximum exercise capacity.

Exercise training will be monitored by an exercise physiologist via a wearable system to measure physical activities and the respective heart rates. A regular feed–back, based on continuous training data interpretation, will be given monthly by video/phone conference in order to motivate the patient and adapt the training prescriptions. In the first year after KTx patients will be seen 4 times face-to-face (2 times a year thereafter), and during these occasions patients will be monitored during a 30 min endurance exercise training.

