### Study endpoints

The primary endpoint of the study will be the 20% reduction in health care costs due to a reduction of hospital utilization of study participants as compared to the control groups (endpoint 3).Increase of adherence for outpatient visits. Goal: Participation in 90% of scheduled visits.Increase of adherence to immunosuppressive therapy. Goals: 1) Coefficient of variation of levels of immunosuppressants <0.4 in 75% of patients. 2) Non-adherence in BAASIS-interview <10% in incident and <20% in prevalent patients / year.Reduction of transplant-associated complications. Goals: 1) Reduction of hospitalization costs by 20% as compared to a control group (primary endpoint) 2) Reduction of graft losses by 25% as compared to a control group.Improvement of cardiovascular fitness and stabilization of weight. Goals: 1) Reduction of hospitalizations caused by cardiovascular complications by 25% as compared to a control sample. 2) Stable weight (weight ± 5%) in patients with a baseline Body Mass Index >18.5 kg/m^2^
Quality of life of the participants will significantly improve. Goals: 1) In the mental subscale of SF-12, 80% of the participants will achieve results that do not differ from norms for the general population. 2) In the physical subscale, 20% will reach results comparable to the general population.Establishment of Standard Operating Procedures (SOPs) including all sectors of the German healthcare system. Finalization of SOPs within 48 weeks of study start.Implementation of an internet-based case file including all sectors of care. Goal: 75% of patients will have used the internet-based case file after 12 months of study start.Implementation and acceptance of telemedicine visits. Goal: 80% of participating physicians will use a telemedicine visit at least once in 80% of their patients within 12 months.

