To evaluate the goals longitudinal and cross-sectional analytic procedures are used. In both, comparisons between the included patients and the control groups are conducted if applicable. Longitudinal analyses will be conducted with regression analyses in mixed models with repeated measures. This approach is feasible to estimate within-person change over time and group differences in within-person change over time. Cross-sectional group comparisons will be analyzed with regression models without repeated measures. All models will be adjusted for possible confounders, such as age of patients, distance to transplant center or co-morbidities. Descriptive statistics will be conducted to illustrate results, achievement of endpoints (see section on endpoints) and sample characteristics. All effects will be tested with a significance level of *p* = .05.

Group differences in within-person change and levels at one point in time will be evaluated with data available for the comparison groups (mainly data from statutory health insurances). For example, in year one after transplantation costs for hospitalizations of incident patients who received their transplantation in 2017 are expected to be lower as compared to the historical comparison group (prevalent patients with transplantation between 2010 and 2016) and as compared to the external control group (with transplantation in 2017 at different transplant centres). Additionally, data on adherence assessed with the BAASIS interview of prevalent patients who are included in the study 12 months after transplantation can be compared to the adherence scores of incident patients in month 12 after transplantation.

For data of the psychosomatic and cardiovascular assessments, the evaluation of process and health status are assessed in regular visits of the participating incident and prevalent patients: Within-person change after transplantation will be analyzed. For example, we would expect positive changes in quality of life in incident and prevalent patients during the study period. We would also expect an increase in usage and acceptability of telemedicine treatments among the nephrologists.

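### The comparison with the external group starts at transplantation for everyone, but participants must first reach enrolment, so failures before enrolment can count only against the controls

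*Protocol article*

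**What the plan says.** **Entry of participants.** Methods/design admits patients with "KTx from 2010 to 2019 that was performed at one of the two kidney transplantation centres in the German state of Lower Saxony" and adds two conditions: a participating insurer and "study participation of the (pediatric) nephrologist responsible for the patient’s follow-up". Incident patients are those transplanted in 2017 to 2019. No enrolment day or maximum delay after surgery is given for them.

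**External controls.** The same section defines this group as "claims data of their insurants who received a kidney transplantation in a non-participating German transplant centre between 2010 and 2019". It sets no condition on being alive, or having a working graft, at any later time.

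**Time origin.** Evaluation and study analyses illustrates the primary cost comparison by saying that "in year one after transplantation costs for hospitalizations of incident patients who received their transplantation in 2017 are expected to be lower" than in external recipients transplanted in 2017. Both groups are therefore counted from surgery. The planned adjustment is for confounders such as age, distance and co-morbidity.

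**Goals.** Study endpoints sets a 20% cut in hospitalization costs (primary) and "Reduction of graft losses by 25% as compared to a control group".

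**The concern.** A participant must have reached enrolment, whereas an external control only had to be transplanted. If follow-up starts at transplantation in both groups, the interval before enrolment carries no deaths among participants, by construction. It also carries no graft losses if patients who have already lost the graft are not enrolled. The same early failures elsewhere remain in the control group.

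This differs from volunteer bias, because it would persist if every surviving patient consented. Adjusting for age, distance or co-morbidity cannot bring back patients who never entered. The article judges selection bias improbable because of centre, nephrologist and insurer coverage, and none of these concerns time of entry.

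At stake is a graft-loss result that could move towards the 25% goal under a programme with no effect, in a study meant to inform standard care.

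**Working it through.** **1. Does the external group include every recipient?** Inputs from Methods/design: 2074 transplantations a year, 10% privately insured, 70% response, years 2010 to 2019.
2074 × 0.9 × 0.7 × 10 = 13,066. Less 1,533 participants: 13,066 − 1,533 = 11,533, the stated size. With the 5% mortality deduction, 13,066 × 0.95 = 12,413 (also stated), but 12,413 − 1,533 = 10,880. So 11,533 counts all recipients, before any deduction for death.

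**2. Is loss before enrolment allowed for in incident patients?** The only deduction is "Assuming a response rate of 80% caused by non-participation of health insurances, private practice nephrologists or patients who decline participation". For adult prevalent patients the same paragraph assumes 5% mortality a year before inclusion. For incident patients there is no such term.

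**3. The cost target.** 20% × 19,000 € = 3,800 €. With SD 10,000 and 286 per group, the standard error is 10,000 × √(2/286) = 836 and 3,800/836 = 4.54. Power is Φ(4.54 − 1.96) = 0.995, as stated. The reference figure covers the first 2 years from transplantation.

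**4. Apparent graft-loss reduction with no true effect.** Input: about 8% graft loss in 3 years (Background). Assumptions: constant hazard; enrolment at month m; early graft losses as well as deaths not enrolled.
Hazard h = −ln(0.92)/3 = 0.02779 per year; F(t) = 1 − exp(−ht).
Apparent reduction at year T = 1 − {[F(T) − F(m)]/[1 − F(m)]}/F(T).
Example, m = 3 months, T = 1: F(1) = 0.02741 and F(0.25) = 0.00692. The participants' risk is (0.02741 − 0.00692)/0.99308 = 0.02063. The reduction is 1 − 0.02063/0.02741 = 24.7%.

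| Enrolment (assumed) | Failed before | Year 1 | Year 2 | Year 3 |
|---|---|---|---|---|
| Month 0.5 | 0.12% | 4.1% | 2.0% | 1.3% |
| Month 1 | 0.23% | 8.2% | 4.1% | 2.7% |
| Month 2 | 0.46% | 16.5% | 8.1% | 5.3% |
| Month 3 | 0.69% | 24.7% | 12.2% | 8.0% |

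**5. Primary cost endpoint.** Let a share f of controls fail before the enrolment point at k times the 19,000 € mean (both assumed). Spurious saving = 19,000 × f(k − 1)/(1 − f).

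| f | k | Spurious saving | Share of 3,800 € |
|---|---|---|---|
| 0.5% | 3 | 191 € | 5% |
| 1% | 3 | 384 € | 10% |
| 2% | 3 | 776 € | 20% |
| 5% | 3 | 2,000 € | 53% |
| 2% | 0.5 | −194 € | −5% |

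The sign changes at k = 1. Early failures that are expensive flatter the programme; costs cut short by death work against it.

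**The case against.** The strongest reply is that the delay is unknown. The eligibility sentence fixes the year and place of surgery, not the day of consent, and the consent procedure may stand in a full protocol that is not shown. Enrolment during the transplant stay would leave little bias. This stands, and it limits the size. It does not align the two groups as the article defines them.

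Several stronger readings are tempting, and the documents do not support them:

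- *Enrolment takes two to three months.* A reader might infer this from "Initiated 2–3 months after transplantation". That phrase describes one exercise module for patients meeting listed criteria. A module that starts after enrolment creates no event-free time, and adherence assessments begin early after transplantation.
- *Every early graft loss is shut out.* No inclusion criterion requires a functioning graft. Exclusion is certain only for deaths before enrolment. Background does name death with a functioning graft among the main causes of graft loss, so these deaths bear on the endpoint.
- *The 3-year graft-loss goal could be met by artefact alone.* If 1, 2 or 3 of the 8 percentage points fell before enrolment, 1 − [(8 − x)/(100 − x)]/0.08 gives 11.6%, 23.5% or 35.6%. No stated figure supports such shares, and a constant hazard gives far less at 3 years.
- *All outcomes are counted from surgery.* The article shows this in one example, about costs. It states no origin for graft loss or cardiovascular admissions, and the analysis plan may set one.
- *The primary endpoint is biased towards the programme.* The direction depends on what early failures cost.

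**Conclusion.** The concern holds for the comparison with the external group. The entry rule, the control definition and the time origin in the cost example are all stated, and together they misalign time zero. Nothing in the article corrects this.

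The direction is clear for graft loss, in favour of the programme, and uncertain for the primary cost endpoint. The size cannot be fixed from the article. The graft-loss figures rest on an assumed enrolment month, a constant hazard and non-enrolment of early graft losses. They would be lower if patients with early graft loss are enrolled, and higher if losses cluster soon after surgery. Only the year-1 figure with enrolment at month 3 comes close to the 25% goal.

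The historical group consists of prevalent participants' own past data. It has a separate survivor-selection problem, which this point does not cover.

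**What to change.** In Evaluation and study analyses, state the enrolment window for incident patients and align time zero for the external comparison in one of two ways:

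1. **Common landmark.** Choose one day after transplantation for both groups. Include only recipients alive with a functioning graft on that day, and count hospital costs, graft losses and cardiovascular admissions from then on. Participants who enrol later enter at their enrolment date.
2. **All eligible recipients.** Analyse every eligible recipient of the two centres from transplantation, whether enrolled or not, against the external group.

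Under the landmark, report costs and events before it separately. In the power paragraph of Methods/design, restate the 19,000 € reference cost for the period used, and check the SD and the 3,800 € target against it.

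**Cost.** No new study visits are needed. Under option 1 the early weeks leave the main comparison, and the external claims must supply dates of death and graft loss. The article plans to take graft loss from claims but does not mention dates of death. Option 2 keeps the early weeks but needs claims for non-enrolled recipients of the two centres, and it dilutes the effect. If only 80% of those analysed were enrolled, a 20% reduction would become 0.8 × 20% = 16%, assuming no effect in the others and equal mean costs.

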Selection bias seems unlikely as the study includes all transplantation centres in Lower Saxony and a large majority of nephrologists in private practice is expected to join the study. The participating statutory health insurances cover more than 75% of the population of this federal state. Several important outcome variables are collected in a highly standardized and reliable way as claims data.

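### The two- and three-year completer counts each omit one year of the stated drop-out, and separately the 487 incident patients do not follow from 31 months at 80% response (minor)

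*Protocol article*

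**What the plan says.** All figures are in the protocol article, section Methods/design. The two centres perform about 210 adult and 15 paediatric transplantations per year, and an 80% response rate is assumed. From this, "we expect to include a total sample of *n* = 487 (*n* = 448 adults, *n* = 39 children/ adolescents) incident patients", and the text gives the recruitment period as 31 months. Recruitment is rolling, with "an assumed 15% drop-out rate per year due to graft loss, death or withdrawal from the study". The text then states that "we expect to obtain data from 286 adults and 26 children/adolescents completing 2 years post-transplant observation", and that 121 adults and 12 children will have three post-transplant years.

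The power paragraph of the same section takes 286 incident adults as its sample size for the first two years. It assumes a 20% reduction from 19,000 €, a standard deviation of 10,000 and a two-sided α of .05, and reports that "a power of .995 was estimated to find the assumed difference". It also subtracts 1,533 study participants when sizing the external comparison group; 1,533 is 487 incident plus 1,046 prevalent patients.

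**The concern.** A patient who completes two years has been exposed to two years of drop-out, and one who completes three years to three. With a 15% yearly rate the retention factors should be 0.85² and 0.85³. The stated counts fit 0.85 and 0.85² instead. The two-year count matters most because it is the sample size behind the primary power statement.

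The incident total also disagrees with the rate, period and response given in the same sentence, and the adult and paediatric parts appear to follow different rules. Recruitment and retention would be judged against targets that the plan's own assumptions do not produce.

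**Working it through.** **Inputs (Methods/design):** 210 adults and 15 children per year; response 80%; recruitment 31 months; drop-out 15% per year; difference 0.20 × 19,000 = 3,800 €; SD 10,000; α .05 two-sided. The number of controls in the power calculation is not stated. Equal groups are assumed because that reproduces the stated power.

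**Enrolment per year:** 210 × 0.80 = 168 adults (14 per month); 15 × 0.80 = 12 children.

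**1. Reproducing the plan's power.** Standardised difference 3,800 / 10,000 = 0.38. With 286 per group, 0.38 × √(286/2) = 4.544, and Φ(4.544 − 1.960) = .995. The stated figure reproduces.

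**2. Reproducing the completer counts (adults).**

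| Count | Stated | One year of drop-out fewer | Full drop-out |
|---|---|---|---|
| Two years, two annual cohorts | 286 | 2 × 168 × 0.85 = 285.6 | 2 × 168 × 0.85² = 242.8 |
| Three years, one annual cohort | 121 | 168 × 0.85² = 121.4 | 168 × 0.85³ = 103.2 |

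**3. Could another end of follow-up explain both?** Let follow-up end T months after recruitment starts. With full drop-out, two-year completers are 14 × (T − 24) × 0.85² and three-year completers are 14 × (T − 36) × 0.85³, for T up to 55.
- 286 at two years needs T ≈ 52.3, which gives about 140 at three years, not 121.
- 121 at three years needs T ≈ 50.1, which gives about 264 at two years, not 286.
- The closest compromise (T = 50.8) gives 271 and 127, each about 5% off.

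With one year of drop-out fewer, T = 48 gives 285.6 and 121.4, matching both.

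**4. Effect on power.** With 243 per group, 0.38 × √(243/2) = 4.189, and Φ(4.189 − 1.960) = .987. For comparison, 80% power needs 109 per group and 90% needs 146. With 243 patients against the stated external group of about 11,533, power exceeds .999.

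**5. Incident total.**

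| | Stated | 31 months, 80% | 32 months, 80% | 31 months, no response rate |
|---|---|---|---|---|
| Adults | 448 | 434 | 448 | – |
| Children | 39 | 31 | 32 | 15 × 31/12 = 38.75 |
| Total | 487 | 465 | 480 | – |

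The adult figure matches 32 months at 80%. The paediatric figure matches 31 months with no response rate applied.

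**6. Children's completers.** The stated 26 at two years is close to 2 × 15 × 0.85 = 25.5, again without the response rate and with one year of drop-out. The stated inputs give 2 × 12 × 0.85² = 17.3. The stated 12 at three years fits neither 12 × 0.85² = 8.7 nor 15 × 0.85² = 10.8; full drop-out at 80% response gives 12 × 0.85³ = 7.4.

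**The case against.** The strongest reply is that 243 and 103 are not fixed by the text. The end of follow-up is not given in words, and the Gantt chart is not visible in the copy reviewed. The two-cohort, 48-month structure is inferred from the numerical match. If all 434 adults could be followed for two years, 434 × 0.85² = 314 would exceed 286. This stands as far as the replacement values go. It does not rescue the stated pair, because no single end of follow-up gives both 286 and 121 under the stated drop-out.

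The adult total of 448 may also be right and the 31 months a miscount. The abstract gives study start as May 2017, and May 2017 to December 2019 counted inclusively is 32 months. That is plausible, but the paediatric 39 and the total of 487 would still not follow.

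Three stronger readings are tempting, and the article does not support them:
- **That the 487 error inflates the power.** It does not. The 286 comes from annual cohorts of 168, not from 487 or 448, and the power analysis covers adults only.
- **That 121 is really the two-year count, so the power is much lower.** Nothing in the text says so, and the power paragraph ties 286 to the first two years.
- **That insurer coverage contradicts the 80% response.** The section on evaluation says that "The participating statutory health insurances cover more than 75% of the population of this federal state". This is a lower bound, and it describes the state's population rather than transplant recipients. The 80% may be optimistic, but it is not contradicted.

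**Conclusion.** Two separate arithmetic errors stand, and both are minor.

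First, 286 and 121 do not agree with the stated 15% yearly drop-out and the labels attached to them. On the two-cohort reading the counts are about 243 and 103, so the plan's figures are too high by about 43 and 18 adults. With equal groups, the power falls from .995 to about .987. This rests on the inferred cohort structure and on equal allocation. The stated conclusion of sufficient power is not overturned.

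Second, and with no bearing on the power, 487 does not follow from 31 months at 80%. The inputs give 465, a difference of 22 patients, or 480 if the period is 32 months.

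**What to change.** - State the end of follow-up in the sample-size text, and recompute the two- and three-year counts with 0.85² and 0.85³ (about 243 and 103 adults if two annual cohorts and one are meant). Alternatively, relabel 286 and 121 as patients entering years 2 and 3.
- Restate the power at the corrected two-year number (.987 at 243 per group), naming the control-group size used.
- Derive the incident total from one recruitment period and one response rate: 465 (434 + 31) at 31 months, or 480 (448 + 32) at 32 months.
- Recompute the children's two- and three-year counts by the same rule.
- Carry the corrected total into the 1,533 participants in the power paragraph (465 + 1,046 = 1,511, or 480 + 1,046 = 1,526) and into the abstract, which repeats 448 and 39.

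The cost is corrected figures and a slightly lower stated power. The design and the planned analyses do not change.
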